### Outcomes

#### Primary outcome

The primary objective of this study is to assess the persistence and long-term health outcomes of PASC symptoms. The diagnosis of PASC will be formally established during the first follow-up visit to ensure accurate identification and differentiation from pre-existing conditions, while long-term health outcomes will be evaluated at the second and third follow-up visits (Table 1). Our diagnostic protocol follows the criteria outlined in the WHO definition (32), and utilizes structured telephone interviews for initial PASC assessments (33, 34). PASC symptoms typically emerge at least 3 months after the initial SARS-CoV-2 infection and persist for a minimum of 2 months. To ensure an accurate diagnosis, symptoms must not have been present in the 180 days before infection (35). The initial follow-up visit, conducted 12 months post-diagnosis, confirms the presence and persistence of PASC symptoms, which are systematically evaluated across multiple organ systems, including respiratory, digestive, cardiovascular, musculoskeletal, and neurological functions, as well as general symptoms such as fatigue and fever. Symptom severity is quantitatively assessed using a four-point Likert scale to provide a structured and standardized evaluation of PASC’s impact on patient well-being (36, 37). To further validate symptom emergence and progression, our follow-up protocol differentiates post-COVID-19 manifestations from pre-existing conditions. Aligned with established research protocols, our multidisciplinary (MDR) team conducts follow-ups to collect comprehensive data on new diagnoses and medical consultations, allowing for the identification of secondary conditions potentially associated with PASC (38).

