ISI score (Adults)	x	x	x	x
EQ-5D-Y (Children 4–15 years)	x	x	x	x
PROMIS (Children 8–17 years)	x	x	x	x
SDQ score (Children 4–17 years)	x	x	x	x

°Baseline Assessment: Conducted at the time of hospitalization for COVID-19 at Gansu Provincial Hospital from 2022 to 2023.

°°Follow-Up Visits: Conducted via structured telephone interviews at three time points from 2024 to 2027.

Visit 1 (24 months post-discharge): PASC diagnosis.

Visit 2 (36 months post-discharge): Long-term outcome assessment.

Visit 3 (48 months post-discharge): Final long-term outcome assessment.

*Demographics: Includes age, gender, ethnicity, marital status (for adults), residential status during infection, education background, personal finances (for adults), work status (for adults), and BMI. These details are tailored to ensure age-appropriateness, with specific personal and professional information omitted for children.

†Environmental/socio-economic Factors: Encompasses sulfur dioxide (SO_2_), nitrogen dioxide (NO_2_), ozone (O_3_), particulate matter 10 (PM_10_), particulate matter 2.5 (PM_2.5_), Normalized Difference Vegetation Index (NDVI), temperature, precipitation, relative humidity, wind speed, per capita GDP, income levels, employment status, job types, education level, and living condition. This comprehensive data helps examine the environmental contexts affecting health outcomes.

‡Symptoms Monitoring: Tracks a wide array of symptoms across various systems.

Respiratory: Difficulty breathing, cough, chest pains.

Digestive: Abdominal pain, diarrhea, nausea, vomiting, loss of appetite, constipation.

Cardiovascular: Palpitations, tachycardia, bleeding.

Musculoskeletal: Arthralgia, myalgia, impaired functioning and mobility.

Nervous System: Headaches, dizziness, “brain fog,” sensory impairments, insomnia, and other sleep difficulties.

Other: Fever, fatigue, skin rashes, irregular menstrual cycles (in females over 12 years of age), erectile dysfunction (in males).

¶Lifestyle Factors: Includes smoking and drinking status, providing insights into behaviors that may influence disease progression and recovery.

**Vaccination Information: Documents the dose and timing of COVID-19 vaccinations, critical for assessing vaccine efficacy and patient immunity.

††Reinfection Data: Tracks instances of SARS-CoV-2 reinfection, including timing and test results (PCR, antigen, self-reported symptoms), to understand immunity and disease dynamics.

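### The written PASC case rule has no latest onset and no reinfection clause, so a symptom that starts after a reinfection and is still present at Visit 1 would be credited to the 2022-23 infection

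*Protocol article*

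**What the plan says.** In the protocol article, the Primary outcome section writes the rule in two parts. The first sets latency and duration: "PASC symptoms typically emerge at least 3 months after the initial SARS-CoV-2 infection and persist for a minimum of 2 months". The second is a look-back: "symptoms must not have been present in the 180 days before infection". The section also says "Our diagnostic protocol follows the criteria outlined in the WHO definition", but does not reproduce that definition. The only separation it describes is from earlier illness: "our follow-up protocol differentiates post-COVID-19 manifestations from pre-existing conditions".

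On timing, the section says "The diagnosis of PASC will be formally established during the first follow-up visit", and the notes to Table 1 give "Visit 1 (24 months post-discharge): PASC diagnosis". The Primary outcome section also contains a different timing: "The initial follow-up visit, conducted 12 months post-diagnosis, confirms the presence and persistence of PASC symptoms".

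Table 1 schedules reinfection at all three follow-up visits, and its note states the purpose: "Tracks instances of SARS-CoV-2 reinfection, including timing and test results (PCR, antigen, self-reported symptoms), to understand immunity and disease dynamics". The Follow-up assessments section repeats that reinfections are tracked. Reinfection is not mentioned in the Primary or Secondary outcomes sections, in any part of Statistical analysis (logistic model, GLMM, GPBoost, causal models), or among the limitations in the Discussion.

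**The concern.** The rule guards the period before the index infection with a specific look-back, but leaves the period after it open. Between month 3 and the diagnostic visit, a participant may be infected again and develop new lasting symptoms. Under the written criteria those symptoms are PASC of the first infection.

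This matters because several exposures belong to the index admission. The Environmental data section matches weather and pollutant data to the patient's location and admission period, and acute severity, laboratory results and treatment come from the hospital record. Symptoms set off by a later infection are not outcomes of that acute episode. Counting them has three possible effects:

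- the prevalence of the primary outcome is too high;
- associations with index-admission exposures are pulled towards the null;
- if reinfection is more common at one level of an exposure, that exposure acquires an association it does not have, or has a real one distorted.

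**Working it through.** **Step 1. Apply the rule to the timeline.** Inputs from the article: latency at least 3 months, duration at least 2 months, visit at 24 months. Infection and discharge are treated as the same month, an approximation.

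- Latest onset that has lasted 2 months by the visit: 24 - 2 = month 22.
- Eligible onset window: 22 - 3 = 19 months.
- With the other stated timing, read as 12 months after infection: 12 - 2 - 3 = 7 months.

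Example: reinfection at month 14, new cough from month 15, still present at month 24, no cough in the 180 days before the 2022-23 infection. Onset is later than month 3, duration exceeds 2 months, the look-back is clear and the symptom is present at the visit. Every written criterion is met.

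**Step 2. Share of counted cases that would follow a reinfection.** The article states no PASC rate, reinfection rate or post-reinfection symptom rate, so there is no figure to reproduce. All three inputs are assumptions:

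- p = true index PASC, 10-20%;
- r = reinfected before the visit, 20-60%;
- q = new lasting symptoms among those reinfected, 5-10%.

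Affected cases as a proportion of the cohort = (1 - p) × r × q. Share of counted cases = (1 - p)rq / [p + (1 - p)rq]. Counts use 4,000 participants, the article's minimum cohort.

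| p | r | q | (1 - p)rq | Counted PASC | Share affected | Of 4,000 |
|---|---|---|---|---|---|---|
| 20% | 20% | 5% | 0.8% | 20.8% | 3.8% | 32 |
| 20% | 60% | 10% | 4.8% | 24.8% | 19.4% | 192 |
| 10% | 20% | 5% | 0.9% | 10.9% | 8.3% | 36 |
| 10% | 60% | 10% | 5.4% | 15.4% | 35.1% | 216 |

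A middle case (p = 20%, r = 30%, q = 10%) gives 0.8 × 0.3 × 0.1 = 2.4%. Counted PASC is then 22.4%, and 2.4 / 22.4 = 10.7% of cases are affected.

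**Step 3. Effect on associations (all values assumed; p = 20%, q = 10%).**

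- *Dilution.* Reinfection is 30% in both groups and the true OR is 1.50. Unexposed: 0.20 + 0.80 × 0.03 = 0.224. Exposed: true risk 0.375 / 1.375 = 0.2727; observed 0.2727 + 0.7273 × 0.03 = 0.2945. Observed OR = (0.2945 / 0.7055) / (0.224 / 0.776) ≈ 1.45.
- *Spurious association.* There is no true effect, and reinfection is 40% against 20%. Observed PASC is 0.20 + 0.80 × 0.04 = 23.2% against 0.20 + 0.80 × 0.02 = 21.6%. OR = (0.232 / 0.768) / (0.216 / 0.784) = 1.10. With 2,000 per group, a two-proportion test gives p < 0.05 about 23% of the time instead of 5%. This calculation ignores the city random intercept in the GLMM.

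**The case against.** The strongest reply is that the point rests on silence. The article condenses a fuller protocol, the latency sentence is hedged by the word *typically*, and the criteria are said to follow a WHO definition that is not reproduced. A reader might infer that the study has decided to count post-reinfection symptoms, or that it will never use the reinfection dates. The documents do not support that: no sentence says either. What stands is narrower. The article spells out its primary-outcome rule, down to a 180-day look-back, and that rule applied as written admits these symptoms.

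A reader might also infer that any two-month symptom after a reinfection is counted, even one that has resolved before the visit. The article does not clearly support this, because the visit is meant to confirm that symptoms are present as well as persistent. Only symptoms still present at the visit clearly qualify, which narrows the problem.

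Nor can it be said that cases after a reinfection are unrelated to the study's exposures. NDVI, per capita GDP, education and comorbidities are lasting characteristics that may bear on symptoms after any infection. The Follow-up assessments section also mentions updating environmental exposures. The dilution argument fits admission-period weather and pollution, acute severity and treatment.

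The list of covariates in Statistical analysis is open-ended, DAGs are planned to identify confounders, and the final covariate set normally belongs in the SAP. So the absence of reinfection from that list is not itself an error. The planned sensitivity analyses concern missing data, measurement error and attrition; none names reinfection. The city intercept affects inference, but does not remove bias in exposures that vary between cities.

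**Conclusion.** The point holds as a gap in the written primary-outcome definition. With no latest onset and no reinfection clause, a symptom that begins after a reinfection and is present at the 24-month visit meets the rule for the index infection, although the dates that could separate such cases are being collected.

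The size cannot be determined from the document. Under the assumed rates, roughly 4-35% of counted cases would be affected: 4-19% if index PASC is 20%, and 8-35% if it is 10%. These figures, and the odds ratios above, are illustrations only. The effect would be smaller if the first visit were at 12 months, because the onset window would be 7 months rather than 19. The article gives both timings and they must be reconciled. The change should be made because it concerns the primary outcome and draws on data already collected, but the documents do not show that the results would be seriously wrong without it.

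**What to change.** In the Primary outcome section:

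1. State that the onset month of each reported symptom is recorded. The 3-month latency rule already requires it.
2. Use the collected reinfection dates to class each PASC case as onset before, or onset after, the first reported reinfection.
3. Report prevalence and the main risk-factor models for index-attributable cases (onset before any reported reinfection) alongside the unrestricted count. Keep both, because a restricted count alone could drop genuine late-onset cases of the index infection.
4. State that recalled onset dates and unreported reinfections limit the split.
5. Reconcile the two stated timings of the first visit, since the choice sets how long participants are exposed to reinfection before diagnosis.

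Whether reinfection should also enter later models as a post-baseline covariate is debatable and can be left to the SAP.

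Cost: a short addition to the case definition, one onset field per symptom if not already on the form, and a second set of the main tables. The restricted analysis will have fewer cases and some misclassification from recall.

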#### Secondary outcomes

The secondary outcomes of this study focus on assessments of the acute infection phase, its progression, the effectiveness of medical management strategies in shaping the trajectory of PASC (38). These assessments are conducted during the follow-up visits, designed to reassess the persistence or resolution of symptoms and evaluate changes in health status since the acute phase of the infection.

The evaluation includes documenting persisting symptoms and identifying any new clinical conditions diagnosed since the initial COVID-19 infection, as well as reviewing medical management strategies such as the reasons for doctor visits and treatments received during the follow-up period. Analysis objectives includes the persistence and progression of symptoms, with a specific focus on respiratory difficulties, overall quality of life, and mental health issues, including anxiety and depression (39). For pediatric populations, the assessment is tailored to specifically monitor the recovery of symptoms relevant to children and adolescents (40), addressing the unique challenges faced by these age groups in the aftermath of COVID-19.

### Variables and data collection

#### Baseline variables

Individual baseline variables will be collected from the Gansu PASC dataset. We gather comprehensive health data during patients’ initial hospitalization for COVID-19. This baseline information serves as a reference to distinguish between pre-existing conditions and symptoms that may be attributed to PASC (41). These variables include demographic factors such as age, gender, ethnicity, marital status, educational background, employment status, and body mass index (BMI). Comorbidities recorded include hypertension, diabetes, respiratory diseases, liver diseases, and other relevant conditions. The Charlson Comorbidity Index (CCI) was adapted using a modified formula to assess morbidity and mortality risks. Conditions were scored as follows: one point for congestive heart failure, chronic pulmonary disease, diabetes, and other conditions; two points for chronic kidney disease and malignant neoplasms; three points for moderate to severe liver disease; and six points for Acquired Immunodeficiency Syndrome (AIDS) (42). Based on the CCI, comorbidities were categorized as mild (0–1), moderate (2–6), or severe (>6). Baseline laboratory assessments included complete blood counts, electrolyte panels, renal and liver function tests, inflammatory markers, and coagulation profiles. Initial treatment protocols involved various medications and supportive care measures, such as oxygen therapy, mechanical ventilation, and immunoglobulin treatments, with emergency interventions including tracheal intubation and cardiopulmonary resuscitation as required.

#### Follow-up assessments

We will conduct telephone follow-ups to diagnose PASC, employing methodologies consistent with those used in major global studies (43, 44). This approach is designed to enhance patient engagement and follow-up compliance, ensuring the inclusion of a broad demographic across diverse geographic locations. Follow-up visits will take place at three time points between 2024 and 2027: Visit 1 (24 months post-discharge) for PASC diagnosis, Visit 2 (36 months post-discharge) primarily for long-term outcome assessment, and Visit 3 (48 months post-discharge) for the final long-term outcome evaluation. During these follow-ups, we will assess the persistence of symptoms and track overall health status, alongside collecting updated information on demographics, environmental exposures, residential status post-infection, lifestyle changes, vaccination history, and hospitalization duration. The monitoring process will also include tracking reinfection cases, post-discharge mortality, the emergence of new symptoms, and changes in health status compared to the initial COVID-19 onset. Consistent with methodologies applied in similar studies (45, 46), our research incorporates patient consultations and provides recommendations for further medical evaluation based on symptoms reported during telephone interviews. However, direct medical interventions are not conducted as part of this study.

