‡‡Recovery Assessment: Includes a single question about recovery perception post-COVID-19, with responses categorized as yes, no, or unsure.

¶¶Comorbidities: Comprehensive data collection on conditions such as hypertension, various cardiovascular and respiratory diseases, diabetes, chronic liver and kidney diseases, metabolic disorders, nervous system diseases, psychiatric conditions, cancers, rheumatism, tuberculosis, and anemia, essential for assessing co-impact on health outcomes.

***Laboratory Test Results: Analysis of blood count, electrolytes, renal and liver functions, inflammatory markers, and coagulation profiles to provide a physiological snapshot of health impacts.

†††Treatment: Detailed record of all treatments administered, including medications, oxygen therapy, mechanical ventilation, ICU care, and other interventions, helping to correlate treatment strategies with outcomes.

‡‡‡Medical management: Information of visiting a doctor for any reason and treatment undertaken during follow-up.

¶¶¶Assessment Tools: Includes the 5-level EQ-5D version (EQ-5D-5L), The Modified Medical Research Council (mMRC) Dyspnea Scale, The Generalized Anxiety Disorder-7 (GAD-7), the Patient Health Questionnaire-9 (PHQ-9), The Fatigue Severity Scale (FSS), The Insomnia Severity Index (ISI), The EuroQol Five-Dimension Youth Questionnaire (EQ-5D-Y) assesses health-related quality of life, The Strengths and Difficulties Questionnaire (SDQ), The Patient-Reported Outcomes Measurement Information System (PROMIS).

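### From Visit 1 onward the calls advise symptomatic participants to seek evaluation, and later diagnoses and consultations are counted with no study-prompted category, so part of any excess in PASC may come from the calls

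*Protocol article*

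**What the plan says.** Four parts of the protocol article bear on this point.

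- **Advice.** Follow-up assessments states that "our research incorporates patient consultations and provides recommendations for further medical evaluation based on symptoms reported during telephone interviews". It adds that the study carries out no direct medical interventions.
- **PASC label.** Primary outcome sets PASC status at the first follow-up visit, from symptoms assessed by structured telephone interview. Symptoms already present in the 180 days before infection do not count.
- **What is counted.** Primary outcome says the team "conducts follow-ups to collect comprehensive data on new diagnoses and medical consultations, allowing for the identification of secondary conditions potentially associated with PASC". Secondary outcomes includes "identifying any new clinical conditions diagnosed since the initial COVID-19 infection" and names as a focus "the effectiveness of medical management strategies in shaping the trajectory of PASC". The Table 1 footnote on medical management reads "Information of visiting a doctor for any reason and treatment undertaken during follow-up", and the item is marked at all three visits.
- **Reasons for care.** Secondary outcomes also mentions "reviewing medical management strategies such as the reasons for doctor visits and treatments received during the follow-up period".

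Table 1 has no item for whether the team gave advice. The sensitivity analyses under Statistical analysis concern missing data and measurement error, and those under the causal inference models are not specified. The limitations in the Discussion cover selection bias, recall bias and attrition, but not detection prompted by the study.

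**The concern.** The information that triggers advice is largely the information that assigns the PASC label. Participants classed as PASC at Visit 1 are therefore more likely than the others to be told to see a doctor. If some act on it, conditions that would have stayed undiagnosed are found more often in PASC, even where underlying disease is equally common. Those diagnoses then enter the data used to name conditions possibly associated with PASC. This is differential ascertainment introduced by the follow-up itself. That the study does not treat anyone does not remove it, because advice alone can change who gets examined.

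The review of medical management is touched in a weaker way. After Visit 1, part of the care recorded may have been sought because the study suggested it, and it would be mixed with care sought in the ordinary course.

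If the advice is not recorded when given, prompted and unprompted events cannot be reliably told apart later. Reconstruction would depend on participants recalling, up to a year afterwards, why they saw a doctor.

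**Working it through.** The plan gives no incidence, detection rate, PASC proportion or uptake of advice, so there is no figure to reproduce. The check has three steps: when the mechanism can act, how large it could be under assumed inputs, and whether dropping prompted events would cure it.

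**1. Window.** Table 1 and Follow-up assessments put Visit 1 at 24 months after discharge, Visit 2 at 36 and Visit 3 at 48. Advice at Visit 1 can affect events reported at Visits 2 and 3, and advice at Visit 2 those reported at Visit 3. Advice at Visit 3 affects nothing that is counted. Diagnoses in months 0–24 and the Visit 1 PASC classification come before any advice. (Primary outcome also places the initial visit at 12 months post-diagnosis. If that were the true timing, the unaffected period would be shorter.)

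**2. Size under assumed inputs.** Let true incidence *t* be the same in both groups. Let *d* be the probability of diagnosis without a prompt, *s* the share of a group that is advised, and *u* the uptake among those advised.

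Diagnosed proportion = *t* × [*d* + (1 − *d*) × *u* × *s*]

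The spurious risk ratio (RR) is this value for PASC divided by its value for non-PASC, so *t* cancels. For months 0–48, half of the unprompted diagnoses are assumed to fall before Visit 1, so the bracket is averaged with *d*.

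Assumed ranges: *d* 0.4–0.8; *s* 0.5–1.0 in PASC and 0.1–0.2 in non-PASC; *u* 0.2–0.5.

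| Scenario | PASC bracket | Non-PASC bracket | RR after Visit 1 | RR months 0–48 |
|---|---|---|---|---|
| Weak: *d* 0.8, *u* 0.2, *s* 0.5 v 0.1 | 0.8 + 0.2×0.2×0.5 = 0.820 | 0.8 + 0.2×0.2×0.1 = 0.804 | 1.02 | 0.810/0.802 = 1.01 |
| Middle: *d* 0.6, *u* 0.3, *s* 0.8 v 0.2 | 0.6 + 0.4×0.3×0.8 = 0.696 | 0.6 + 0.4×0.3×0.2 = 0.624 | 1.12 | 0.648/0.612 = 1.06 |
| Strong: *d* 0.4, *u* 0.5, *s* 1.0 v 0.2 | 0.4 + 0.6×0.5×1.0 = 0.700 | 0.4 + 0.6×0.5×0.2 = 0.460 | 1.52 | 0.550/0.430 = 1.28 |

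Now assume 1,000 PASC and 3,000 non-PASC participants and *t* of 10% or 20%. The chance that a two-sided 5% test shows a false excess in PASC after Visit 1 is about 4% in the weak scenario (both values of *t*), 13% or 22% in the middle one, and 82% or 98% in the strong one. With no bias, the chance of a false excess in that direction is 2.5%.

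**3. Dropping prompted events.** Some prompted diagnoses would have been made anyway. Take *t* = 15%, *d* = 50%, all PASC participants and no others advised, and 40% uptake.

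- All events kept: detection in PASC is 0.5 + 0.5×0.4 = 70%, so 0.15×0.7 = 10.5% against 0.15×0.5 = 7.5%. The odds ratio is (0.105/0.895)/(0.075/0.925) = 1.45.
- Every diagnosis in those who took up advice dropped: 0.15×0.6×0.5 = 4.5% against 7.5%. The odds ratio is (0.045/0.955)/(0.075/0.925) = 0.58.

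The true odds ratio is 1, and it lies between the two.

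**The case against.** The strongest reply is that the article already reviews reasons for doctor visits, which is where an entry such as advised by the study team would appear, and that a tick-box for advice is form-level detail an article may leave to the full protocol. This stands in part. It would be wrong to say that nothing about the origin of a visit is collected. What can be said is that no study-prompted category is specified and nothing stated links a new diagnosis to earlier advice. The article does describe both the prompt and the outcome it affects, and discusses other biases without mentioning this one.

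A reader might infer something stronger: that the calls do create an excess of new conditions in PASC, and that the planned comparison is invalid. The documents do not support that, for three reasons.

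- No formal PASC versus non-PASC test of new-condition rates is stated. The models described take PASC presence, severity, risk factors and recovery as their subject. Calling a condition associated with PASC implies some comparison, but the article does not define one.
- Advice follows symptoms, not the PASC label. Participants whose symptoms predate infection may be advised without being classed as PASC, which dilutes the contrast.
- The size rests wholly on assumed inputs, and at the weak end it is negligible.

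It is also fair to object that who suggested a visit does not alter which treatment was received. The effect on the medical-management aim is therefore plausible, but it is not quantified here.

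**Conclusion.** The point holds in a limited form. Following the plan as written makes detection of new conditions after Visit 1 depend on reported symptoms, and so largely on PASC status, and no stated item or analysis addresses this. Some of any excess in PASC between Visits 1 and 3 may be produced by the calls. If PASC participants are advised more often, and advice only adds diagnoses, the direction is toward more diagnoses in PASC. The documents cannot settle the magnitude; the illustrated range goes from trivial to material. The conclusion assumes that some participants act on the advice and that Visit 1 takes place at 24 months. This is a cheap improvement to data collection and reporting, not an error that undermines the study.

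**What to change.** - **At each call**, record whether advice to seek evaluation was given, the symptom or score that triggered it, and the date.
- **At the next call**, record the date of each consultation or new diagnosis and whether it followed study advice.
- **In reporting**, show new diagnoses dated before Visit 1 separately, as free of study prompting. Show later events with and without prompted ones, and present the two as bounds. The restricted analysis should not be called the corrected answer, because it can reverse the bias.
- **In the Discussion's limitations**, name study-prompted detection.

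The practice of giving advice does not change. The cost is two or three extra fields per call, slightly longer interviews and one extra analysis with fewer events. The fields need to be in place when advice is given, because the information cannot be reliably rebuilt afterwards.
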